**Effect of polyethylene film and artificial teardrops versus normal saline on the incidence of superficial ocular disorders in unconscious patients: a prospective randomized triple-blinded three-arm clinical trial**

**Background:** Polyethylene covers are claimed to be useful in preventing ocular surface diseases (OSD); however, evidence of their clinical efficacy is limited. This clinical trial aims to compare the effect of polyethylene film and artificial teardrops versus normal saline on the incidence of OSD in unconscious patients. This paper summarizes the study protocol.

**Method:** The design of the planned study is a multicenter randomized blinded three-arm clinical trial. Although we need 25 patients in each arm, anticipating a total attrition rate of 20%, a total of 90 patients will be selected and included in the study, 30 patients for each arm. We will set up three arms ‘A’, ‘B’, and ‘C’ in which each eye of a patient will be considered for one of three interventions: artificial teardrops, polyethylene covers, or normal saline eye drops by tossing a coin. Then, each eligible patient will be allocated to one of the three arms by permuted block randomization. All patients are unconscious so, their blinding does not apply. Both the eye observer and the analyzer will be unaware of the type of interventions. The patients’ eyes will be examined based on the Corneal Fluorescein Staining Pattern. The collected data will be analyzed by SPSS-16 software at a 95% confidential level.

**Discussion:** The results of this study will contribute to the developing pieces of evidence for a safe, effective, and accessible eye care intervention for preventing the incidence of OSD in comatose patients.

**Keywords**: Coma, Infectious Diseases, Eye, Intensive Care Units, Nursing Care, Patients.

1. **Introduction**

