**Assessment of eligibility (n=…)**

## Permuted block randomized allocation (n=90)

## (T0)

## Baseline measurement

**Arm** **C** (n=30)

- Received polyethylene cover (Left eye) & artificial teardrops (Right eye)

**Arm** **A** (n=30)

- Received artificial teardrops (Left eye) & normal saline (Right eye).

**Arm** **B** (n=30)

- Received polyethylene cover (Left eye) & normal saline (Right eye)

Analyzed (n=30)

Analyzed (n=30)

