## Analysis

## (T1)

## 5 days following T0

Patients completed interventions C **(n=…)**

- Leaving follow-up (= 25%)

Patients completed interventions A **(n=…)**

- Leaving follow-up (= 25%)

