**Analyzed (n ≥ 25 patients)**

- Left eyes (n ≥ 25)
- Right eyes (n ≥ 25)

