**Analyzed (n ≥ 25 patients)**

- Left eyes (n ≥ 25)
- Right eyes (n ≥ 25)

Patients completed interventions B **(n=…)**

- Leaving to follow-up (= 25%)

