**Figure 1 CONSORT flow diagram**

- 1. ***Sample size calculation***

The sample size is calculating according to the formula below.

$$n=\left[ \frac{\left( Z_{1-\alpha/2}\sqrt{p_{1}\left( 1-p_{1} \right)} \right)+\left( Z_{1-\beta}\sqrt{p_{2}\left( 1-p_{2} \right)} \right)}{d} \right]^{2}$$

With an 80% power and a 2-sided significance level of α = .05, and the probability of incidence of OSD of a study in which 3.6% (= p_1_) of patients had a positive fluorescein test in the simple eye ointment group and 20.2% (= p_2_) of patients had a positive fluorescein test in the eyelid taping group [5], the number of people needed in each group is 25. Anticipating a total attrition rate of 20%, a total of 90 patients will be included in the study, 30 patients for each arm.

- 1. ***Participants and recruitment***

Patients in the three ICUs in university-affiliated hospitals located in Malayer, Iran, will be recruited:

*2.4.1. Inclusion criteria*

- Newly being admitted to the ICUs;
- Having 18 years of age or older;
- Being comatose (with a Glasgow Coma Scale (GCS) less than or equal to 8 of 15);
- Undergoing mechanical ventilated;
- No trauma in the areas of the face and eyes;
- No history of chronic disease, electrolyte imbalance, cataract surgery or glaucoma;
- Absence of blinking (less than five times per minute); and
- Having a healthy cornea.

*2.4.2. Exclusion criteria*

- Presence of consciousness or natural blinking reflexes;
- Requiring cardiopulmonary resuscitation during the trial;
- Getting discharged from ICUs to the other centers or death.
  1. ***Implementation of the Interventions***

All patients will be received routine eye care. Routine eye care is consisted of eye irrigation with sterile normal saline when necessary (PRN) in all our ICUs. In addition to this usual care, prior to applying the planned interventions, the participants’ eyelids and surrounding skin will be gently irrigated by sterile normal saline and sterile gauze in the same way. The interventions are as below:

- For the intervention with artificial teardrops, while pulling down the lower lid of the patient’s eye to form a V pocket, two Tearlose (Miscellaneous) drops will be applied every six hours.
- For the intervention with normal saline, two drops of saline 0.9% will be applied in the same manner and dose.

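### The attrition allowance is miscalculated and inconsistent: 30 per arm leaves 24 evaluable patients at the 20% in the text and 22 to 23 at the 25% in Figure 1, not the promised 25 or more

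*Protocol*

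**What the plan says.** The abstract and the sample size section (2.3) agree. The abstract has "Although we need 25 patients in each arm, anticipating a total attrition rate of 20" per cent. Section 2.3 says "the number of people needed in each group is 25" and continues: "Anticipating a total attrition rate of 20%, a total of 90 patients will be included in the study, 30 patients for each arm".

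Figure 1 starts from the same total, "Permuted block randomized allocation (n=90", with 30 in each arm. At day 5 it gives a different loss. Arms A and C carry "Leaving follow-up (= 25" per cent and arm B carries "Leaving to follow-up (= 25" per cent. Below that, every arm has a box reading "Analyzed (n ≥ 25 patients", with at least 25 left and 25 right eyes.

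Section 2.4.2 lists the exclusion criteria. Among them are resuscitation while the trial is running and "Getting discharged from ICUs to the other centers or death". Table 1 schedules the staining examination only at baseline and at day 5.

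**The concern.** There are three defects on the face of the document.

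- **The inflation step.** Adding 20% to the required number is not the same as allowing for 20% loss. The required number has to be divided by the fraction expected to remain.
- **The rate.** The text uses 20% and Figure 1 uses 25%, so a reader cannot tell which loss the design is meant to withstand.
- **The promise.** Figure 1 cannot have both 25% loss from 30 and at least 25 analysed.

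The number of analysable patients behind the power statement is therefore not delivered under either rate. The Discussion says that attrition was allowed for in the sample size, and this was not done correctly.

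A secondary matter concerns labels. Resuscitation during the trial and death in the ICU can occur only after enrolment, so they are not eligibility criteria. Listing them as exclusions invites the removal of randomised patients, and Figure 1 points the same way by moving from patients who completed the interventions to patients analysed.

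**Working it through.** **Inputs.** Required evaluable per arm: 25 (abstract, section 2.3). Randomised: 30 per arm, 90 in total (abstract, section 2.3, Figure 1). Attrition d: 0.20 (abstract, section 2.3) or 0.25 (Figure 1, all three arms). Event proportions: 3.6% and 20.2% (section 2.3). Test for incidence: McNemar (Data Analysis).

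**1. Reproduce the plan's figure.** 25 × (1 + 0.20) = 30 per arm and 3 × 30 = 90. This matches exactly, so the multiplication explains the stated number.

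**2. Correct inflation,** n / (1 − d):
- at 20%: 25 / 0.80 = 31.25, so 32 per arm and 96 in total;
- at 25%: 25 / 0.75 = 33.3, so 34 per arm and 102 in total.

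**3. What 30 per arm delivers,** 30 × (1 − d):
- at 20%: 30 × 0.80 = 24;
- at 25%: 30 × 0.75 = 22.5, so 22 or 23.

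**4. Loss at which 25 survive.** 1 − 25/30 = 16.7%. No section states this rate.

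**5. Chance of meeting the floor.** If losses are independent, the number retained in an arm is binomial with 30 trials and probability 1 − d. P(at least 25) is 43% at 20% loss and 20% at 25% loss. For all three arms together, 0.4275³ = 8% and 0.2026³ = 0.8%.

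**6. Effect on power.** Each arm gives paired eyes, so I used the exact two-sided McNemar test at 0.05 within one arm. Let p11 be the probability that both eyes stain. The discordant probabilities are then 0.202 − p11 and 0.036 − p11. The protocol gives no between-eye correlation, so p11 is an assumption. I ranged it from 0 (correlation −0.10) through independence (0.036 × 0.202 = 0.0073) to its maximum of 0.036 (correlation 0.38). Power is summed over all possible discordant counts.

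| Pairs per arm | Power over the range |
|---|---|
| 22 | 14–16% |
| 23 | 17–18% |
| 24 | about 20% |
| 25 | about 22% |
| 30 (nobody lost) | 31–38% |

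The maximum-correlation case can be checked by hand. All discordant pairs then go one way, and significance needs at least 6 of them (2 × 0.5⁶ = 0.031). Power is the binomial chance of 6 or more among n pairs with probability 0.202 − 0.036 = 0.166, which gives 0.197 at n = 24 and 0.145 at n = 22.

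**7. Is attrition the main cause of low power?** No. Power is already about 22% at the full 25 pairs. The 25 itself does not reproduce: the printed formula gives 17.9 with the proportions as labelled and 32.3 with them swapped, and the standard formula for two independent proportions gives 59 per group.

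**The case against.** The strongest reply is about size. At the 20% given in the text, the shortfall is one patient per arm (24 against 25), or 30 randomised against 32. Power moves from about 22% to about 20%, which changes no decision. This stands. The defect is an inconsistency that is cheap to correct, and the larger weakness in the figure of 25 should not lend it weight. The reply does not cover Figure 1, where 25% loss and at least 25 analysed out of 30 cannot both be true.

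A reader might also infer that the plan discards every patient who leaves before day 5. The document does not support that as fact:
- No analysis set is defined, and handling of early exits may be left to an SAP that is not at hand.
- Figure 1 suggests that completers are analysed, but it also carries two boxes giving 30 as the number analysed, whose place in the diagram is unclear from the extracted text.
- The discharge criterion names only transfer to other centers, not every ICU discharge.
- The consciousness criterion could be read as applying at screening.

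Nor can it be said that obtainable outcome data are being thrown away on any known scale. Exits are not split by cause. A slit-lamp reading after death is not feasible, and one around resuscitation may often be impracticable. The share that could be recovered is unknown.

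Finally, keeping early exits with an earlier examination is not free of difficulty. Both eyes of a patient have the same exposure time, so the paired comparison stays fair. The Kruskal–Wallis comparison of severity is made between groups, and unequal exposure is not cancelled there.

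**Conclusion.** The arithmetic error and the contradiction are certain on the protocol's own figures. Thirty per arm leaves 24 evaluable at 20% loss and 22 to 23 at 25%, and the analysed floor of 25 holds only if loss is at most 16.7%. The 25% in Figure 1 is the larger of the two discrepancies.

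The cost in power is a few percentage points: about 22% at 25 pairs, 20% at 24 and 14–16% at 22. These figures assume the plan's 3.6% and 20.2%, an exact two-sided McNemar test within one arm, and any between-eye correlation those proportions allow. Correcting the allowance would not bring power near 80%, because the 25 has a separate problem.

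The labelling of resuscitation during the trial and death as exclusion criteria is a secondary, real fault. That all early exits are dropped is only an inference. Overall this is a point that should be fixed, not one that by itself invalidates the design.

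**What to change.** - **One rate.** Use a single attrition figure in the abstract, section 2.3 and Figure 1.
- **One evaluable number.** Replace the floor of 25 with what 30 per arm delivers: 24 at 20%, or 22 at 25% (rounding 22.5 down). If 25 evaluable is to be kept, 32 per arm (96 in total) is needed at 20%, or 34 (102) at 25%.
- **Matching power.** Restate power at that number for the planned McNemar test and give the assumed between-eye correlation. On the plan's proportions this is about 20% at 24 pairs and 14–16% at 22. Deal with the derivation of 25 separately, and do not present this correction as restoring 80%.
- **Labels.** Move events that can occur only after enrolment from the exclusion criteria to reasons for early exit. Keep in the within-patient analysis any such patient who has a post-baseline staining examination. State that the recoverable share is unknown and that exposure time will differ between patients in the Kruskal–Wallis comparison.

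**Cost.** The first three items are wording, plus a less favourable stated number, unless enrolment is raised by 6 or 12 patients. The fourth is also wording if it uses only examinations that exist. Adding examinations at exit would take staff time and would change the outcome from staining at day 5 to staining at exit or day 5, which would have to be stated.

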**Table 1. Study measures, source of measurement, and time of assessment.**

| **Construct** | **Questionnaire** | *Assessment times | | |
| --- | --- | --- | --- | --- |
|  |  | **S** | **T0** | **T1** |
| Demographic | Socio-demographic data | * | - | - |
| Clinical characteristics | Clinical history | * | - | - |
| Incidence of Ophthalmic Surface Diseases | The Corneal Fluorescein Staining Pattern | - | * | * |
| Severity of Ophthalmic Surface Diseases | The Corneal Fluorescein Staining Pattern | - | * | * |

*Assessment times: S= Screening, T0= baseline, T1= 5 days after the allocation.

*2.6.1 Primary outcome*

The incidence and severity of OSDs will be assessed with the Corneal Fluorescein Staining Pattern. The cornea will be examined at the slit lamp with a blue filter between four and eight minutes following fluorescein instillation. Punctate epithelial erosions (PEE) will be counted and scored from zero to six, the maximum possible score for each cornea. Grade 0 for no PEE, grade 1 for 1-5 PEE, grade 2 for 6-30 PEE, and grade 3 for more than 30 PEE. A score of severity will be added when the PEE is seen in the central 4mm diameter portion of the cornea, one or more filaments occurred anywhere on the cornea, or one or more patches of confluent staining, including linear stains, if found anywhere on the cornea.

- 1. ***Data Analysis***

In addition to descriptive statistics, the assumption of normality for numerical variables will be examined with the K-S test. Patients’ characteristics will be compared across the three treatment groups, using the Chi-Square test for categorical variables (sex, and type of injury) and one-way ANOVA for numerical variables (age). The incidence of OSD will be compared across the three treatment groups by McNemar’s test and the severity of the OSD by the Kruskal–Wallis test.

1. **Discussion**

This paper describes the evidence-based interventions added to the routine eye care for unconscious patients hospitalized in ICUs. It also presents the study protocol to compare the effectiveness of three methods of eye care, artificial teardrops, polyethylene covers, or normal saline eye drops using a prospective randomized triple-blinded three-armed clinical trial.

Patients who are admitted to Intensive Care Units (ICUs) usually experience failures in one or more vital organ systems such as respiratory, neurologic, and cardiovascular systems accompanied by many other complications which may be resulted in insufficient eye care. Insufficient eye care of ICU patients can increase the risk of serious eye problems such as corneal abrasions and ulceration, infectious keratitis, and even corneal perforation and loss of vision [10, 11]. There are strong agreements upon the existing diversity of the OSD risk factors for patients in ICUs. The comatose patients are suffering from tear film reduction and misaligning over the ocular surface, tear components dilution due to lack of blinking, lid incomplete closing, and lid or conjunctival edema occurring with the use of a ventilator and in the prone position [3-8].

There are many pieces of evidence for eye care which included a wide range of interventions such as eye washing with normal saline solution, using lubricating ointments or teardrops, moisturizing the chambers by applying a polyethylene eye cover (PEC), swimming goggles, and eye shields, closing the eyelid with pads or patch, transparent tape, or tarsorrhaphy. But, there is no clear evidence as to which of these interventions represent the ideal eye care for ICU patients to prevent OSDs [3, 4, 8, 10, 12-17].

Although polyethylene eye covers have been suggested as the most effective intervention[4, 18] the lubricants and taping of the lids are only advised for eye care in the intensive care unit [19]. In many ICUs included ours, the standard care has been only giving in a daily washing of eyelids with normal saline and sterile gauze and application of ocular lubricants at least twice per day [20]. So, there is a large space to generate evidence from high-quality researches to employ the evidence-based nursing practice. This randomized triple blinded three-arm clinical trial can work in this task.

The main strength of this study is to our knowledge, this would be the first randomized clinical trial to examine the incidence and severity of the OSDs among comatose patients in three groups: routine care (Normal saline), evidence-based care (eye-cover and eye lubricant). This study can provide high-quality pieces of evidence for future evidence-based nursing practice. The study limitation would be due to the probability of the attrition rates which been taken into account in the sample size calculation.

1. **Conclusion**

We present the design of our study aimed to promote an evidence-based nursing practice for critically ill patients’ eye care. The results of this study will contribute to the growing research on exploring the best practices. If the expected results are achieved, this could be considered as an important step in the implementation of such nursing care to enhance evidence-based practice in critically ill patients to prevent OSDs.

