- For the intervention with a polyethylene eye cover, 2.5-inch square pieces of thin plastic film will be put from the above of the eyebrow to the cheekbone and fixed by hypoallergenic paper tape.
  1. ***Outcome***

Assessments will be conducted using the statistical software SPSS version 16.0 for windows (SPSS Inc., Chicago, IL), setting the p-values at < 0.05. The measures used and measurements in the study are described in Table 1.

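### Incidence and severity share the primary outcome unranked, and the plan implies four tests at an unadjusted 0.05 with no order among them

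*Protocol*

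**What the plan says.** - **Primary outcome (Protocol, Section 2.6.1).** One heading, in the singular, covers two outcomes: "The incidence and severity of OSDs will be assessed with the Corneal Fluorescein Staining Pattern". Neither is put first, and there is no section on secondary outcomes. The Aim also names both. The title and the sample size concern incidence only.
- **Sample size calculation.** One two-group comparison of positive fluorescein tests: "With an 80% power and a 2-sided significance level of α = .05". The assumed rates are 3.6% (p1, ointment) and 20.2% (p2, taping), both taken from one cited study. The result is 25 per group, raised to 30 per arm and 90 in total.
- **Threshold.** The Outcome section states "setting the p-values at < 0.05". The abstract states "The collected data will be analyzed by SPSS-16 software at a 95% confidential level". Neither place mentions an adjustment or a test order.
- **Data Analysis.** "The incidence of OSD will be compared across the three treatment groups by" McNemar's test. Severity is compared by one Kruskal–Wallis test.
- **Study design.** Each arm holds a different treatment pair within the patient: tears and saline in A, cover and saline in B, cover and tears in C.

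**The concern.** A protocol should say which result decides the trial. This one names two outcomes for that role and sized only one of them. Its incidence test handles two paired conditions, so it cannot compare three treatments in one step. The workable reading is one McNemar test within each arm. Adding the severity test gives four tests of a primary outcome, each at 0.05, with no order or decision rule.

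As written, a report could rest its claim on whichever outcome or treatment pair reached 0.05. The Conclusion ties achieving the expected results to adopting the care in practice, so the missing rule matters.

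**Working it through.** **1. The plan's own figure.** The printed sample-size formula with p1 = 0.036, p2 = 0.202, d = 0.166, z = 1.960 and 0.842:

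n = [(1.960 × 0.1863 + 0.842 × 0.4015) / 0.166]² = [(0.3651 + 0.3379) / 0.166]² = 17.9, so 18.

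The stated 25 is not reproduced. That is a separate matter. What counts here is that the calculation covers one comparison of incidence at two-sided 0.05, with nothing for severity or for a second or third pair.

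**2. Number of tests.** Three McNemar tests (A, B, C) plus one Kruskal–Wallis test make four. The plan contains no pairwise severity tests.

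**3. Nominal error if each test has size 0.05.** The arms contain different patients, so the three incidence tests are independent.

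- Three incidence tests: 1 − 0.95³ = 14.3%.
- Four tests, if independent: 1 − 0.95⁴ = 18.5%.

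Severity uses the same staining score on the same eyes, so its test is positively related to the incidence tests, and 18.5% serves as a ceiling. With no assumption about dependence the bound is 4 × 5% = 20%.

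**4. Actual size of three McNemar tests.** With n pairs and discordance probability q, the size of one test is Σₘ Bin(m; n, q) × P(reject | m discordant pairs, split ½ : ½). For three arms it is 1 − (1 − size)³. Incidence and between-eye correlation are assumptions, because the protocol gives no correlation and only a literature range for incidence.

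Worked case: incidence 20.2%, independent eyes, 25 pairs. Then q = 2 × 0.202 × 0.798 = 0.322.

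- Uncorrected: 0.0438 per test, and 1 − 0.9562³ = 12.6% for three.
- Exact: 0.0192 per test, and 1 − 0.9808³ = 5.6% for three.

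Over latent correlation 0–0.6 and 25–30 pairs:

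| Assumed incidence | Three tests, uncorrected | Three tests, exact or continuity-corrected |
|---|---|---|
| 10–60% | about 9–14% | about 1–8% |
| 3.6% | about 1–5% | close to 0 |

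**5. Adding severity.** A null simulation of the paired-eye design (4,000 runs per scenario, 25 or 30 patients per arm, incidence 12–60%, correlation 0–0.6) gave 11.5–15.9% for all four tests with uncorrected McNemar and 2.7–10.9% with exact McNemar. The three incidence tests alone gave 10.3–14.4% and 0.8–7.9%. Severity therefore adds only a few points. One reason is that Kruskal–Wallis on correlated eyes was itself at or below its level (1.4–5.0%).

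**The case against.** Several objections have force.

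- **No trial-wide 5% is stated.** A reader might infer that the trial's false-positive rate is well above a 5% it promised. The 0.05 is the level of one two-group calculation and a per-test threshold, and no family-wise rate is given. With exact or continuity-corrected McNemar the actual rate can be near or below 5%. That stronger reading is not supported.
- **Six tests are not planned.** A reader might count three pairwise severity tests as well and reach 1 − 0.95⁶ = 26.5%. The protocol plans one omnibus severity test, so this figure does not apply.
- **Three tests are implied, not written.** This is true, and the count follows from the arm structure and from what McNemar's test can do. The mismatch between test and design is the more basic fault, and both are repaired together.
- **No rule says that any one positive test is a success.** Also true. The fault is that no rule is given at all.
- **Incidence is plainly the lead outcome.** The title and the sample size suggest so, but Section 2.6.1 and the Aim say otherwise.
- **Multiplicity may be handled in a statistical analysis plan.** None is shown, and one may set an adjustment. The choice of primary outcome still belongs in the protocol, and this protocol names two.

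It might also be argued that 25 per group already contains an adjustment, since the printed formula at 0.05/6 gives 24.96. The text states 0.05, so this is a coincidence.

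**Conclusion.** The point holds as a fault of specification with a moderate effect on error. The protocol has two unranked primary outcomes, only one of them sized, and an unadjusted 0.05 for what amounts to four unordered tests. The 14.3% and 18.5% assume that every test runs exactly at its nominal level. The enumerated ranges rest on the assumed incidence and between-eye correlation, equal treatments and no difference between left and right eyes. The McNemar version is the largest unknown: uncorrected, the error is roughly two to three times 5%, while exact or corrected it may need little repair. In neither case does the protocol say which result decides the trial.

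**What to change.** 1. In Section 2.6.1, name incidence at T1, the outcome that was sized, as the single primary outcome. Make severity the first secondary, tested only if incidence is significant.
2. In Data Analysis, replace McNemar across three groups with a named global 2-df test that respects the eye pairing, at 0.05. Examples are conditional logistic regression with the patient as stratum, or a score test on discordant pairs.
3. Interpret the three pairwise contrasts, each at 0.05, only if the global test is significant. State the version of the pairwise test. With three treatments this is a closed procedure, so it holds the family-wise error of the incidence contrasts near 5% without splitting alpha. In simulation the gated error under the null was about 3–4%.

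**Cost.** This is more than wording, because McNemar's test has no 2-df form for three treatments and the incidence analysis must be rewritten. The gate also costs power. With 25 pairs per arm and an assumed between-eye correlation of 0.3, simulated power for cover against saline (3.6% against 20.2%) fell from about 49% to 44%. With tears at 10% it fell from 48% to 39%. The loss is roughly 5–9 percentage points.

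A simpler alternative keeps three McNemar tests at 0.05/3 = 0.0167 each, with incidence as sole primary (1 − 0.9833³ = 4.9%). By the pooled two-proportion formula that raises the need from 59 to 79 per group.

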This is a prospective randomized triple-blinded three-armed clinical trial. We set up three arms ‘A’, ‘B’, and ‘C’ in which by tossing a coin, each eye of a patient will be allocated to one of three interventions: artificial teardrops, polyethylene covers, or normal saline eye drops. The groups will be as the following:

- Group “A”: patients received artificial teardrops for the left eyes and normal saline for the right eyes.
- Group “B”: patients received polyethylene cover for the left eyes and normal saline for the right eyes.
- Group “C”: patients received polyethylene cover to the left eyes and artificial teardrops to the right eyes.

Then, each eligible patient will be allocated to one of the three arms by permuted block randomization.

The study will be approved by the Research and Technology Vice-chancellor after confirming the proposal by the Research Ethics Committee at Hamadan University of Medical Sciences and registering in the Iranian Registry of Clinical Trials. We will conduct the study according to the ethical principles of the Helsinki Declaration of 2013 and follow the CONSORT 2010 statement (http://www.consort-statement.org). The study design is shown in Figure 1.

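### Severity is scored on both eyes of each patient but tested by Kruskal-Wallis, which assumes independent groups; unit and comparison factor are not stated, and no reading gives a valid direct comparison of all three interventions.

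*Protocol*

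**What the plan says.** The Study design section gives each patient two interventions, one per eye, in three pairings:

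- Arm A: "patients received artificial teardrops for the left eyes and normal saline for the right eyes".
- Arm B: "patients received polyethylene cover for the left eyes and normal saline for the right eyes".
- Arm C: "patients received polyethylene cover to the left eyes and artificial teardrops to the right eyes".

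Section 2.6.1 makes incidence and severity of ocular surface disease the primary outcome. Severity is "scored from zero to six, the maximum possible score for each cornea". No patient-level score is defined. Figure 1 counts the analysed eyes by side within each arm: a line beginning "Left eyes (n ≥ 25" and a matching line for right eyes, from the same 25 or more patients.

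The Data Analysis section then says: "The incidence of OSD will be compared across the three treatment groups by McNemar"'s test, "and the severity of the OSD by the Kruskal"–Wallis test. One sentence earlier, for sex, type of injury and age, patients' "characteristics will be compared across the three treatment groups". Those are patient characteristics, so there the groups can only be arms A, B and C. For severity the section does not say whether the groups are arms or interventions, or whether the unit is the eye or the patient.

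**The concern.** One sentence gives the same eyes a paired test for incidence and an independent-samples test for severity. The risk factors listed in the Introduction and Discussion (loss of blinking, tear film impairment, ventilator-related oedema) act on the whole patient, so the two eyes of a patient are likely to be positively correlated. A test that ignores this uses the wrong variance. The direction of the error depends on how the eyes are grouped, and the protocol leaves that open.

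This is not a detail left for a later analysis plan. The protocol names a specific test for part of its primary outcome, and that test does not fit the paired-eye design. At stake are a severity comparison that loses power, one that gives too many false positives, or one that does not directly answer the stated aim of comparing polyethylene film, artificial tears and saline.

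**Working it through.** **Inputs.** From the protocol: three arms and their pairings, at least 25 patients analysed per arm, a 0–6 score per cornea, two-sided alpha 0.05. Assumed: the between-eye rank correlation r, which the protocol does not give; 0.3 to 0.9 is used. The protocol reports no figure for this test, so there is none to reproduce.

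**Eyes grouped by intervention.** With n patients per arm, each intervention has 2n eyes, and any two interventions share one arm of n patients.

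- Variance of each mean: s²/(2n). Covariance of two means: n·r·s²/(2n)² = r·s²/(4n).
- Variance of a difference: 2·s²/(2n) − 2·r·s²/(4n) = (s²/n)(1 − r/2). The test assumes s²/n.
- All three contrasts are affected equally, so the statistic behaves as (1 − r/2) times chi-square on 2 df. The 5% critical value is 5.991, so true size = exp(−5.991 / [2(1 − r/2)]).
- r = 0.3: exp(−5.991/1.7) = 0.029. r = 0.6: exp(−5.991/1.4) = 0.014. At r = 0.6 the assumed variance is 1/0.7 = 1.43 times the true one.

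**Eyes grouped by arm, both eyes pooled.** The variance of an arm mean is s²(1 + r)/(2n), against an assumed s²/(2n). True size = exp(−5.991 / [2(1 + r)]).

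- r = 0.3: exp(−5.991/2.6) = 0.100. r = 0.6: exp(−5.991/3.2) = 0.154.

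**Simulation under the null.** 10,000 trials per setting, 25 patients per arm, 0–6 scores cut from a correlated latent normal, 40% of eyes positive:

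| Latent correlation | By intervention | By arm, eyes pooled | By arm, patient mean | By arm, left eye only |
|---|---|---|---|---|
| 0.3 | 0.035 | 0.088 | 0.049 | 0.050 |
| 0.5 | 0.024 | 0.111 | 0.048 | 0.046 |
| 0.7 | 0.014 | 0.152 | 0.048 | 0.049 |
| 0.9 | 0.007 | 0.200 | 0.052 | 0.051 |

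With 12% of eyes positive the directions are the same and the errors milder at the low end: 0.037 to 0.010 by intervention, 0.066 to 0.171 by arm with eyes pooled. A within-patient test on left-right rank differences had size 0.037 to 0.050 across all settings.

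**What the versions of correct size compare.**

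- Left eyes receive tears, polyethylene, polyethylene in arms A, B, C, and never saline. Right eyes receive saline, saline, tears, and never polyethylene. Each side covers two of the three interventions.
- Patient means compare pairs. With additive effects, A − B = (tears − polyethylene)/2, A − C = (saline − polyethylene)/2 and B − C = (saline − tears)/2. An arm difference has variance s²(1 + r)/n; doubling it to recover the full treatment difference gives 4s²(1 + r)/n. At n = 25 and r = 0.3 that is 4 × 1.3/25 = 0.208 s², against 0.85/25 = 0.034 s² for the difference between intervention means.

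**Cost of adjusting for side.** Generalised least squares, 25 patients per arm, continuous approximation: adding a left/right term multiplies the variance of polyethylene minus saline by 4.1 at r = 0.3 and 5.6 at r = 0.6. At r = 0.6 it becomes 0.110 s², compared with the 1/25 = 0.040 s² that treating eyes as independent would assign.

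**The case against.** A reader might infer that the p-value is wrong however the sentence is read. The protocol does not support that. It never says that both eyes enter one test as separate observations, and Figure 1 lists left and right eyes separately. By arm, with one value per patient or one side at a time, Kruskal-Wallis keeps its size. The inflated false-positive rate therefore depends on pooling that the protocol does not state.

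A reader might also infer that a by-arm result cannot be traced to a treatment because arm differences are half-differences. That does not follow: under additivity the three half-differences map one-to-one onto the three treatment contrasts. What they lose is precision and directness.

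It can fairly be added that the aim and the Discussion speak of comparing interventions, so the by-intervention reading is the more natural one, and there the error is conservative. The sizes depend on an assumed correlation and on how many eyes are positive.

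All of this stands, and it limits the point without removing it. The by-intervention reading still wastes the pairing, the readings with correct size do not compare the three interventions directly, and the preceding sentence uses the same phrase for the arms, so the anti-conservative version is not excluded.

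**Conclusion.** The severity analysis is wrong as written and should be corrected, because it concerns part of the primary outcome.

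- By intervention, the p-value is too large: true size about 2.9% at r = 0.3 and 1.4% at r = 0.6.
- By arm with both eyes pooled, it is too small: about 10% and 15%.
- By arm with one value per patient or one side at a time, the size is correct but the comparison is of pairs of interventions, or of two interventions per side.

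The directions require only a positive between-eye correlation, which is plausible here; the sizes rest on the assumed values of r. At r = 0 both pooled versions have about the nominal size. The documents do not support a blanket statement that every reading gives an invalid p-value.

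**What to change.** State that intervention, not arm letter, is the comparison factor for severity. Replace Kruskal-Wallis with an analysis of the 0–6 score at T1 that treats the patient as the cluster and uses all three arms. Either of these would do:

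- an ordinal GEE or mixed model with intervention as a three-level factor; or
- a within-patient rank test on left-right differences, with a multiplicity rule if it is done arm by arm.

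Use eye side as a sensitivity analysis, not a required covariate, because of the four- to sixfold variance cost on polyethylene versus saline. Without that term, this contrast relies on there being no left-right difference, which the report should say. The T0 score is optional: a healthy cornea is an entry criterion, so it should vary little.

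The cost is analysis wording and slightly more analysis work; design and data collection do not change. One limit should be planned for. At the rates used in the Sample size calculation, 150 analysed eyes would give between 150 × 0.036 ≈ 5 and 150 × 0.202 ≈ 30 positive eyes. If few eyes are positive, a collapsed score or the rank-based version may be needed, and the protocol should name that fallback in advance.
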